## Abstract

**Background:**

In December 2019, 27 cases of pneumonia, of unknown cause, were identified in the province of Hubei (China). The WHO declared the situation as a Public Health Emergency of International Concern, and it was finally declared a global pandemic on March 11, 2020. The Spanish Government obliges the entire population to remain confined to their homes, with the exception of essential basic services, to stop the spread of COVID-19. Home isolation implies a notable physical deconditioning. Telerehabilitation methods have reported positive experiences, and we propose to study in affected patients of COVID-19, due to the general house confinement of the entire Spanish population.

**Methods:**

Patients will be recruited in the regions of Andalusia, Murcia, and Valencia (Spain). Patients will remain confined to their homes, and there, they will carry out their assigned exercise program, which will be controlled telematically. Evaluators will attend to carry out all measurements at the beginning, during, and end of the study, telematically controlled. The patients will be randomly divided into three groups, two of them will perform a home exercise program (breathing exercises or non-specific exercises for muscle toning) and the third group will perform sedentary activities, using mental activation techniques, and will act as a sham group. We will evaluate respiratory variables and other variables of the physical state through physical tests, effort, and perceived fatigue. The data will be statistically analyzed, and the hypotheses will be tested between the groups, using the SPSS software, v.24, considering a 95% confidence interval.

**Discussion:**

We will analyze the results, in terms of the level of fatigue and perceived exertion, physical health, and maintenance of respiratory activity of two types of exercise programs, toning and respiratory, applied in patients affected by COVID-19 during the period of home confinement. We intend to investigate a field not previously studied, such as the repercussion of carrying out a toning and respiratory exercise program in these patients, in historical circumstances that no one had previously observed in Spain, since the general population has never been forced to remain confined in their homes, due to a pandemic infection, by a coronavirus (COVID-19). Observing the effects that these two home exercise programs could produce in patients infected with COVID-19, we will try to better analyze and understand the mechanisms that are associated with the worsening of breathing in this type of patient.

**Trial registration:**

Brazilian Clinical Trial Registry RBR-6m69fc. Registered on March 31, 2020.

## Background

In December 2019, 27 cases of pneumonia, of unknown cause, were identified in Hubei (China) [1]. On January 7, 2020, the Chinese authorities identified a new virus, which was called SARS-CoV-2, and since then, it is commonly known as COVID-19 [2]. Subsequently, on January 30, 2020, the WHO declared the situation as a Public Health Emergency of International Concern [3], and it was finally stated a global pandemic on March 11, 2020 [4]. Since March 14, 2020, the Spanish Government decreed the state of alarm, which implied house confinement for the entire population, with the exception of essential basic services, to stop the spreading of COVID-19 [5].

This virus is characterized by its contagion capacity, which, as it has been established, can occur through three routes: the respiratory route, by direct contact, and through feces (although more research is needed in this route) [6]. It has been estimated that the incubation period is 5.2 days for a 95% confidence interval (CI) [4.1–7.0], and the basic number of reproduction R0 is 2.2 for a 95% CI [1.4–3.9] [7].

As of May 24, 2020, countries that are considered the most affected are the USA (1,568,448 cases; 94,011 deceased), the UK (257,158 cases; 36,675 deceased), Italy (229,327 cases; 32,735 deceased), Brazil (330,890 cases; 21,048 deceased), and Spain (235,290 cases; 28,678 deceased), being according to the WHO, the total of 5.206.614 confirmed cases and 337.736 confirmed deaths by COVID-19, presenting cases in 216 countries or territories [7, 8]. The main signs and symptoms described by recent studies [9–11] are fever (98%), cough (76%), and myalgia or fatigue (44%); atypical symptoms have also been identified: sputum (28%), headache (8%), hemoptysis (5%), vomiting (5%), diarrhea (3%), and dyspnea in approximately half of the patients. In addition to lymphopenia, identified in 63% of cases, pneumonia is present in all patients. Complications include acute respiratory distress syndrome (29%), acute heart injury (12%), and secondary infections (10%). In addition, other symptoms more striking such as chemosensory dysfunction have also been described [12]. Some patients had at least one underlying disease (such as hypertension, chronic obstructive pulmonary disease), and many of them require treatment in intensive care units (ICU) [9–11].

It has been estimated that 80% of the patients will present mild symptoms (without hospital admission). The remaining 20% will need medical care, and 5% of them will require admission to the ICU [10, 13]. The average time from onset of symptoms to recovery is 2 weeks when the disease has been mild and 3–6 weeks when the disease has been severe or critical [14]. The WHO recommends, for 80% of patients who do not require hospital admission, the need for very restrictive home isolation and confinement in individual rooms at home to avoid the spreading of the virus [15]. The total isolation of these patients requires non-face-to-face medical attendance, performing telematic control to monitor the evolution of the patient affected by COVID-19.

Home isolation implies a notable physical deconditioning, not only at the musculoskeletal level, but also implies negative metabolic changes [16, 17]. It could trigger peaks in type II diabetes, which could lead to worsening of the clinical picture in patients affected by COVID-19 [18] and repercussions on emotional state [19]. Physical activity programs have reported beneficial effects in maintaining muscle mass and strength [20] and prevents metabolic and nutritional decompensations caused by inactivity [21]. The implementation of a physical activity program in patients with mild symptoms of COVID-19 could achieve breathing benefits, reducing the rate of aggravation and hospital admissions in these patients.

Our study aims to verify and validate the efficacy of a telerehabilitation program, through therapeutic exercise at the respiratory level, and the maintenance of vertebral and thoracic muscle tone, in patients affected by COVID-19. There is evidence on the efficacy of domiciliary exercise-based treatments in patients with respiratory disorders, and based on this, this could be the therapeutic method of choice to allow the treatment and supervision of patients affected by COVID-19 during home confinement [22–24]. Telerehabilitation has begun to be implemented in other rehabilitation fields, such as cardiac rehabilitation, cancer rehabilitation, neurological rehabilitation, and spinal cord injuries [25–27]. Some studies have pointed out the effectiveness of these methods [28, 29]; however, the last systematic reviews and meta-analyses highlight the limited evidence, mainly due to the lack of high-quality research studies [30, 31]. In general terms, telerehabilitation methods have been reported as positive experiences by patients [32] and can represent an important way to reduce associated healthcare costs [30]. Nonetheless, in this case, the reasons for implementing telerehabilitation are not economic, but of necessity, due to the general house confinement of the entire Spanish population established to avoid the spreading of the virus.

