## Objectives

### Primary objective

The aim of our study is to analyze the respiratory effects of a therapeutic exercise program in patients affected by the coronavirus (COVID-19), during the period of home confinement.

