### Procedure for adverse effects

Participants will be daily assessed through a phone call by a member of the study team, who will ask for possible adverse events. This follow-up will be performed through a checklist translated and adapted from “Criteria for clinical evaluation during telephone follow-up of home care” published by SEMFYC [33], and it can be checked in Additional file 2. In addition, a telephone number will be provided to the participants. If any complication or doubt, they should contact the member of the study team, and in the function of episode features, they will be informed of the procedure to follow.

The Trial Steering Committee is made up of three researchers external to the research group; they will meet weekly and analyze the ongoing results of the research; they have the power to partially or completely paralyze the course of the study. This study does not contemplate any intervention of public organisms for its development.

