### Outcome measures

The data will be collected by personnel attached to the research group who have previously been instructed in the procedures to follow and do not know the group to which the patients belong; the captures sent by the patients will be stored and classified; the evaluators will transfer the numerical values to an excel table. The images sent by the patients and the excel table are encrypted, and only the evaluators and the main researchers have access to it. This information is updated through a security cloud. All outcomes will be measured daily using WhatsApp or by email for 21 days.

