## Discussion

This article presents a detailed description of a randomized controlled trial designed to analyze the results in terms of the level of fatigue and perceived exertion, physical health, and maintenance of respiratory activity of two types of exercise programs, toning and respiratory, applied in patients affected by COVID-19 during the period of home confinement. We intend to investigate a field not previously studied: the repercussion of carrying out a toning and respiratory exercise program in these patients, in historical circumstances that no one had previously observed in Spain, except the Spanish flu of 1918 where scientific knowledge and intervention capacity were very limited, since the general population had never been forced to remain confined at home due to a pandemic infection. Because some of these patients develop severe symptoms associated with respiratory distress, we consider that this study could be of interest in public health, to prevent worsening of the respiratory status of these patients, and so that we could understand the mechanisms that produce these serious alterations, which in many cases require hospitalization and the use of mechanical ventilation. We propose two types of treatments, one using breathing exercises exclusively and the other based on non-specific muscle toning exercise.

Measuring the effects that these two home exercise programs could produce in patients infected with COVID-19, we will try to better analyze and understand the mechanisms that are associated with worsening of breathing in this type of patient. Our results seek to analyze whether respiratory muscle stimulation, or vertebral/thoracic tonic musculature, is a protective factor in maintaining the health of these patients, and if together with cardiovascular stimulation they could have a specific influence on the prevention of severe respiratory disturbances suffered by some of these patients.

We have designed a randomized, controlled, double-blinded clinical trial, with the aim of contributing to increasing scientific knowledge on this matter, so new lines of future research could be developed.

The results will be communicated to the Spanish health authorities internally and to other relevant groups through publications in medical journals.

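### Preventing worsening and admission is a stated rationale and a Discussion aim, but no outcome records it, and admitted patients may go uncounted when losses are 15% or less

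*Protocol article*

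**What the plan says.** All references are to the protocol article.

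- **Rationale.** The Background says that a physical activity programme in mild cases could bring benefits for breathing, "reducing the rate of aggravation and hospital admissions in these patients".
- **Discussion.** The study is offered as a means "to prevent worsening of the respiratory status of these patients". The results are meant to show whether muscle stimulation is protective and whether, together with cardiovascular stimulation, "they could have a specific influence on the prevention of severe respiratory disturbances suffered by some of these patients".
- **Formal objective.** "The aim of our study is to analyze the respiratory effects of a therapeutic exercise program". The secondary objective compares respiratory effects between the three arms. Neither objective names admission or progression.
- **Outcomes.** There are seven: VASF, FEV1, PEF, 6MWT, 30STST, MD12 and the Borg Scale. The SPIRIT figure caption lists the same seven. On timing: "All outcomes will be measured daily using WhatsApp or by email for 21 days".
- **Monitoring.** "Participants will be daily assessed through a phone call by a member of the study team, who will ask for possible adverse events". The call follows a checklist in Additional file 2, adapted from the same source as the moderate/severe criteria under Exclusion criteria.
- **Losses.** Interventions, Sampling and sample size calculation, and Statistical analysis all make intention-to-treat conditional on losses above 15%.

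**The concern.** The outcome list is given in full and does not match the question posed in the Discussion. Two consequences follow.

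First, whatever the trial finds on fatigue, lung function or walking distance, it will have no designated result on admission or progression. The Background and Discussion invite readers to expect one.

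Second, all seven outcomes need a patient who can blow into a spirometer, walk, stand up from a chair or complete scales at home every day. A patient sent to hospital will probably stop doing so. With intention-to-treat switched off at losses of 15% or less, such patients may be dropped from the comparison without appearing as an event. A programme with more deteriorations could then look better among those who remain. This matters within the trial too: under the Sham program section, sham patients later receive whichever programme showed the greater health benefit, and that choice would rest on outcomes that do not count deterioration.

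**Working it through.** **1. The plan's own figure.** Inputs from Sampling and sample size calculation: one-sided alpha 0.05, power 90%, SD 0.125, difference 0.10, losses 15%.
n = 2 × (1.645 + 1.282)² × (0.125/0.10)² = 26.8, so 27 per group. 27/0.85 = 31.8, so 32. The stated 32 is reproduced. The sizing rests on VASF alone; admission plays no part in it.

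**2. The intention-to-treat trigger.** 15% of 114 is 17.1. Seventeen losses are 17/114 = 14.9% (no trigger); eighteen are 15.8% (trigger). The threshold is not stated per arm. As an illustration, 8 losses in one arm and 2 in each of the others give 12/114 = 10.5%. Intention-to-treat is not triggered, although the arms lose 8/38 = 21% and 2/38 = 5%.

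**3. What could be hidden.** Suppose the patients lost in step 2 all worsened, and that their final VASF would have been k standard deviations worse than that of patients who stayed. Leaving them out hides a between-arm difference of (8/38 − 2/38) × k × 0.125.
- k = 1: 0.158 × 0.125 = 0.020
- k = 2: 0.158 × 2 × 0.125 = 0.039

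Against the design difference of 0.10 this is about 20% to 39%. The values of k and the loss pattern are assumptions.

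**4. Event counts and power.** The article gives no admission rate for mild home patients. Its figure of 20% needing medical care refers to all cases. Assume sham rates p1 of 2% to 20%, halved to p2 in both exercise arms, with 38 per arm. Expected events are 38 × (p1 + 2 × p2). Two-sided 5% power for one pairwise comparison is Φ[(p1 − p2 − 1.96 × SE0)/SE1], where SE0 = √(2p̄(1 − p̄)/38), p̄ is the mean of p1 and p2, and SE1 = √{[p1(1 − p1) + p2(1 − p2)]/38}.

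| p1 vs p2 | Expected events, three arms | Power at 38 per arm | n per arm for 80% power |
|---|---|---|---|
| 2% vs 1% | 1.5 | 5% | 2319 |
| 5% vs 2.5% | 3.8 | 8% | 906 |
| 10% vs 5% | 7.6 | 13% | 435 |
| 15% vs 7.5% | 11.4 | 18% | 278 |
| 20% vs 10% | 15.2 | 23% | 199 |

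The normal approximation is rough at these counts, but the order of magnitude is clear. Even in the last row, 15.2/114 = 13.3%, so admissions alone would not be expected to reach the 15% trigger.

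**5. Precision.** At 10% vs 5%, SE1 = √[(0.09 + 0.0475)/38] = 0.060. The risk difference is 5 percentage points, with a 95% half-width of 1.96 × 0.060, about 12 points.

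**The case against.** The strongest reply has five parts.

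- **Prevention is one conditional motive.** The Background says could, alongside deconditioning and the need for remote care, and the formal objectives concern respiratory effects. This stands. It would be wrong to infer that the trial is built on prevention alone. But the Discussion goes further than motivation when it says what the results seek to analyse.
- **Respiratory worsening is measured.** FEV1, PEF and MD12 are recorded daily. This also stands, so a reader should not infer that the trial can say nothing about worsening. The gap is limited to referral, admission and progression beyond what a patient at home can record.
- **Nothing says that worsened patients are removed.** Correct: their loss is an inference, and values from before admission would exist. The exclusion of hospital-referred patients stands under Sample selection and reads as an eligibility rule; whether it also applies after randomisation is not stated. The inference is still likely to hold, given what the outcomes demand of the patient and the conditional intention-to-treat rule.
- **The data may not be on hand.** Additional file 2 is not shown. Several moderate/severe criteria (oxygen saturation, blood pressure, auscultation) have no matching device or examination in the sections on adverse effects and outcome measures. So it cannot be assumed that every criterion is already captured or that the change is free.
- **Safeguards exist, and adverse-event reporting can sit in a fuller document.** Daily calls and a weekly external steering committee protect patients. They do not supply a between-arm result on the question the Discussion asks.

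**Conclusion.** The point holds in a limited form. The article states prevention of worsening and admission as a rationale and as something its results should inform, but provides no outcome that records referral, admission or progression. Up to 17 of 114 losses leave intention-to-treat switched off, so admitted patients may be neither analysed nor counted. The possible distortion of VASF is moderate: about 20% to 39% of the design difference under the deliberately unequal losses shown above.

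A reader might infer that adding the outcome would let the trial test prevention. It would not: power is about 5% to 23% under the assumed rates. Its value is to show the counts and to expose unequal dropout. The conclusion rests on three assumptions: that admitted patients stop sending data, that the analysis follows the 15% rule as written, and that control rates lie between 2% and 20%, a range the documents do not supply. The change should be made, but the point does not undermine the formal objectives.

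**What to change.** 1. Add a descriptive secondary or safety outcome for all randomised patients, by day 21: hospital referral or admission, or progression to moderate/severe disease as far as the existing daily call and checklist can ascertain it. State which criteria the call can and cannot establish.
2. Report it by arm as counts and risk differences with 95% confidence intervals, with no confirmatory test.
3. Analyse all randomised patients in their allocated arm whatever the loss rate. Keep the values recorded before worsening, and say how such patients enter the analyses of the seven listed outcomes.
4. State whether the exclusion of hospital-referred patients under Sample selection is an eligibility rule only.
5. Limit the prevention statements in the Background and Discussion to what this outcome can show.

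The cost is a change to protocol and analysis wording and, if the checklist does not already record referral, one extra item on a call that is made every day. The downside, to be stated openly, is wide intervals: a half-width of about 12 percentage points at assumed rates of 10% and 5%.

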## Objectives

### Primary objective

The aim of our study is to analyze the respiratory effects of a therapeutic exercise program in patients affected by the coronavirus (COVID-19), during the period of home confinement.

### Secondary objective

The secondary objective is to compare the respiratory effects obtained among patients affected by the coronavirus (COVID-19), after the application of a respiratory exercise program (REP), compared to those who perform a non-specific toning exercise program (NTEP) and a to sedentary control group performing a sham program, during the period of house confinement.

## Methods/design

### Trial design

The trial design is a randomized, controlled, parallel, double-blind, three-arm clinical trial of treatment.

### Sample selection

Patients will be recruited through a text message transmitted on social network (WhatsApp); they will be contacted with a general message informing of the possibility of participating in a physiotherapy study; all those interested will be informed later in greater detail, in the regions of Andalusia, Murcia, and Valencia (Spain). Therefore, any patient resident in the autonomous communities of Andalusia, Murcia, and Valencia may participate in this research. The messages will be sent to positive cases through PCR tests (polymerase chain reaction) classified by the epidemiology services of each region. In terms of privacy, only patients who have validated their contact for information and research services to the corresponding epidemiology services will be contacted. Later, they will be selected according to the listed eligibility criteria. The study will take place at the selected patients’ home, where the evaluators will attend to carry out all measurements at the beginning, during, and end of the study. All measurements will be instructed and telematically controlled by the study evaluator, who will provide patients the necessary assessment materials, which are described below (the “Outcome measurements” section).

Only mild cases will be recruited, so all patients must be confined at home. We will exclude those patients who required derivation to hospital care. The criteria are based on those published by the Spanish Society of Family and Community Medicine (SEMFYC) and can be checked on the “Exclusion criteria” section [33].

### Inclusion criteria

The following are the inclusion criteria:
Age 18–75 yearsPatients with positive polymerase chain reaction (PCR) testPatients who are affected by the coronavirus (COVID-19) and are in home confinement

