### Exclusion criteria

The following are the exclusion criteria:
Patients with chronic lung conditionsPatients with chronic kidney diseasePatients affected with chronic neurological disordersPatients suffering from hypertension and cardiovascular conditions without medical treatmentPatients affected with grade III osteoporosisPatients affected with acute phase of rheumatologic disordersPatients affected with acute phase of disc abnormalitiesPatients who have had respiratory conditions in the last 12 monthsPatients who have recent musculoskeletal disorders and who are not fully recovered from their injuriesPatients who have received physical therapy treatment in the last 3 monthsPatients affected with chronic mental and/or psychological disturbancesRed flags for serious conditions (night pain, severe muscle spasm, loss of involuntary weight, symptom mismatch)Patients classified as moderate/severe cases based on the following criteria [33]:
Respiratory rate ≥ 30 brpmSpO2 < 92%Cardiac rate > 125 bpmHypotension (SBP < 90 mmHg or DBP < 60 mmHg)Severe dyspnea (minimal effort or rest)Signs of respiratory compromise (cyanosis, use of accessory muscles)HemoptysisAltered alertness (lethargy, acute confusion, disorientation)Inability to orally intake due to unintended vomiting or a significant number of bowel movements (≥ 10 per day) suggesting dehydration or hydroelectric disturbancesSignificant impact on the general conditionHigh clinical suspicion of pneumonia requiring radiography, based on worsening of dyspnea, more than 7 days with fever, respiratory rate higher than 22 brpm, and alteration in auscultation. Punto 3.

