Visual Analog Scale Fatigue (VASF), for fatigue measurement [38]. Patients participating in the study will indicate the intensity of their fatigue by means of the VAS through the smartphone application called “Visual Scale” (Apple Store and Google Play). They will have to signal in a horizontal line where they would place their fatigue, being 0 “no fatigue” and the 10 would be “the worst imaginable fatigue”. VASF will be controlled telematically by the evaluators through the Smartphone application. The evaluator will ask the patient to indicate their level of VASF in the “Visual Scale” application and to take a screenshot of the smartphone to obtain the established value for VASF, which is calculated as the average value of two attempts. The patient must send the VASF screenshot daily to the evaluator, via WhatsApp or email.Forced expiratory volume in 1 s (FEV1). The Piko-1 spirometer device will be sent to the home of each patient by post, and a telematic control of its use will be carried out. The evaluator will ask the patient to indicate their level of FEV1 assessed by the Piko-1 device, twice each time. FEV1 obtained values by patients must be sent to the evaluator, via WhatsApp or email. We will calculate the means of each 2 measurements, assessed by patients every day [39, 40].Peak expiratory flow (PEF). The evaluator will ask the patient to indicate their level of PEF assessed by the Piko-1 device, twice each time. After obtaining the values, patients will send them to the evaluator, via WhatsApp or email. We will calculate the means of each 2 measurements, assessed by patients every day [41].Six-Minute Walk Test (6MWT). The 6MWT will be performed by all patients in their home, under the telematically supervision of a physiotherapist. All patients will receive the same instructions before the walk and will be encouraged by the physiotherapist who repeated set phrases every minute during the walk. The distance covered during the test will be recorded in meters telematically by the patient’s smartphone. Patients will be allowed to stop and rest during the test, but they will be instructed to resume walking as soon as they felt able to do so. Patients will send the results of the 6MWT screenshot daily to the evaluator, via WhatsApp or email [42].Thirty Seconds Sit-To-Stand Test (30STST). Evaluators will ask patients to place a straight-backed armless chair, with a hard seat, which will be stabilized by placing it against a wall, considering floor to seat height will be between 45 and 50 cm. Seated participants will be asked to come forward on the seat until their feet will be flat on the floor and to fold their upper limbs across the chest, without moving it during all tests. Patients will be then instructed to stand up all the way and sit down once without using the upper limbs. Patients will start in the seated position on the chair and, upon command telematically, they will stand up, and then they will return to sitting as many times as they could, in a 30-s time period [41–43]. The evaluators will control this test telematically by videoconference.Multidimensional Dysphnoea-12 (MD12) Spanish version [44]. The MD12 questionnaire will be self-administered and will be performed at the end of the 6MWT. Patients will send the results of the MD12 screenshot daily to the evaluator, via WhatsApp or email.Borg Scale (BS). The Borg Scale, of perceived effort, measures the entire range of effort that the individual perceives when exercising. This scale gives criteria to make adjustments to the intensity of exercise, that is, to the workload, and thus forecast and dictate the different intensities of exercise in sports and medical rehabilitation. The BS will be completed by patients at the beginning of each session and after completing the exercise program, as well as at the end of the tests, every day (6MWT, 30STST). Patients will send the results of the BS screenshot daily to the evaluator, via WhatsApp or email [45, 46].

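### The entry criteria do not define current illness, so recovered mild cases can qualify; this dilutes the VASF comparison, and the planned ANOVA ignores time since onset

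*Protocol article*

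**What the plan says.** The Inclusion criteria section has three entries: age 18–75, a positive PCR test with no date attached, and patients "who are affected by the coronavirus (COVID-19) and are in home confinement". The Exclusion criteria are long and detailed. They remove moderate and severe cases and many comorbidities, but not people who have recovered. The only illness duration in them, "more than 7 days with fever, respiratory rate higher than 22 brpm, and alteration in auscultation", is part of the exclusion for suspected pneumonia and is not an entry window.

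Under Sample selection, "The messages will be sent to positive cases through PCR tests (polymerase chain reaction) classified by the epidemiology services of each region", and only mild cases are recruited. The Background states that "the Spanish Government decreed the state of alarm, which implied house confinement for the entire population", from March 14, 2020, and that "The average time from onset of symptoms to recovery is 2 weeks when the disease has been mild". Trial status puts recruitment between March 31 and April 30, 2020. Each programme runs for 21 days.

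The sample size rests on VASF, where 0 means no fatigue. The Statistical analysis section compares outcomes by one-factor ANOVA or Kruskal-Wallis. It labels this contrast intragroup, but a one-factor ANOVA compares groups and I read it that way. No covariate is named.

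**The concern.** Nothing in the written criteria separates a patient in the first days of illness from one whose illness is over. The PCR may be of any date. Confinement, read as the national measure, applied to ill and well alike. Entry takes further time after the first contact: the patient replies, receives fuller information, and needs a spirometer that goes "The Piko-1 spirometer device will be sent to the home of each patient by post".

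Two things are at stake:

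- **Dilution.** A patient who reports almost no fatigue at baseline has almost no room to improve on VASF, whichever programme is assigned. Each such patient pulls the mean difference towards zero.
- **Noise.** Patients at different points of a self-limiting illness recover by different amounts over 21 days for reasons unrelated to allocation. An unadjusted ANOVA leaves this spread in the error term.

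**Working it through.** **Step 1: can a recovered patient meet the criteria?** Take a mild case with onset on March 14, the day confinement began. Adding the protocol's average of 14 days gives recovery on about March 28. Recruitment opens on March 31, three days later. This person has a positive PCR, is on a regional list and is confined like everyone else. Only an unstated meaning of *affected* would keep them out.

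**Step 2: reproduce the sample size.** Inputs from Sampling and sample size calculation: difference 0.10, SD 0.125, one-sided alpha 0.05, power 0.90, losses 15%.

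- Standardised difference: d = 0.10 / 0.125 = 0.8
- n per group = 2 × (1.645 + 1.282)² / 0.8² = 26.8, so 27 evaluable
- With losses: 27 / 0.85 = 31.8, so 32, which is the protocol's figure

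The calculation treats the 0.10 difference as the average over all enrolled patients.

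**Step 3: evaluable number under actual enrolment.** The protocol enrols at least 38 per group: 38 × 0.85 = 32.3, so 32 evaluable. This is the number to use for power, rather than 27.

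**Step 4: dilution.** Let p be the share already recovered at baseline. The documents do not give it, so it is assumed and shown as a range. Suppose those patients show no VASF effect and the SD stays at 0.125. Then:

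- diluted difference = 0.10 × (1 − p)
- d = 0.8 × (1 − p)
- noncentrality = d × √(32/2) = 3.2 × (1 − p)

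Power of the one-sided two-sample t-test at alpha 0.05:

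| p | Difference | d | Noncentrality | Power |
|---|---|---|---|---|
| 0 | 0.100 | 0.80 | 3.20 | 0.94 |
| 15% | 0.085 | 0.68 | 2.72 | 0.85 |
| 30% | 0.070 | 0.56 | 2.24 | 0.72 |
| 50% | 0.050 | 0.40 | 1.60 | 0.48 |

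The normal approximation agrees to within 0.01.

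**Step 5: how much the extra enrolment absorbs.** By the normal approximation, power stays at 0.90 while 3.2 × (1 − p) ≥ 1.645 + 1.282 = 2.927, that is p ≤ 1 − 2.927/3.2 = 0.085. Going from 32 to 38 per group therefore covers a recovered share of up to about 9%.

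**The case against.** The strongest reply is that the criterion is in the present tense, and *are affected* may mean currently ill. Sample selection links confinement to being a mild case, and the Background describes strict isolation in individual rooms for patients who do not need hospital care. Confinement might therefore mean disease isolation rather than lockdown. That reading is possible, but the article also uses the word for the national measure, and no symptom, repeat test or date settles it. What stands is that active illness is undefined. A reader might infer that recovered patients were enrolled routinely, but the documents do not show that.

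A reader might also infer that recovered patients had nothing left to improve. The text does not support this across outcomes. The Background names physical deconditioning as a concern, and the Discussion aims at maintaining function and preventing worsening. The 6MWT and 30STST have no symptom floor. MD12 is completed after the 6MWT, and Borg is also scored after exertion. The floor argument is made here for VASF only.

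Third, the groups are randomised, so time since onset is balanced in expectation. This objection stands: the consequence is lost power and precision, with some chance imbalance, and not systematic bias.

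Fourth, the fixed SD is a simplification. Mixed stages of illness may raise the SD, while patients clustered at the floor may lower it. The net direction is not established.

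Finally, the posted spirometer might suggest that delivery delay falls after randomisation. The article does not state the order of the two, so no error is shown there.

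**Conclusion.** The point holds in limited form. The written criteria do not exclude mild cases who have recovered, and the planned between-group test makes no allowance for time since onset. For VASF the likely result is a diluted difference and a noisier comparison. Power falls below the planned 0.90 once the recovered share exceeds about 9%, and is about 0.85, 0.72 or 0.48 at 15%, 30% or 50%, against 0.94 with none.

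These figures rest on an assumed recovered share, no VASF effect in recovered patients, an SD fixed at 0.125, 32 evaluable per arm, and the plan's own one-sided two-group test. They describe sensitivity and do not estimate what happened. They do not carry over to the walking, sit-to-stand or post-exertion measures.

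**What to change.** **Main change.** Record for every patient the date of symptom onset, or of the positive PCR if asymptomatic. Replace the unadjusted one-factor ANOVA with an ANCOVA on group, the baseline value of the outcome and days since onset, with both covariates specified in advance. The cost is one date field. This deals with the noise and with chance imbalance, and it lets the report show how far into the illness patients entered. It does not restore an effect diluted by patients at the floor.

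**Optional change.** To limit the dilution, tie *affected* in the Inclusion criteria to a stated maximum time since onset or PCR, chosen by the investigators against the 2-week figure in the Background. A symptomatic-only rule is not needed, and it would make a PCR-dated window for asymptomatic patients pointless. The cost is a smaller eligible pool, which matters when 114 patients are to be recruited in one month. If that cost is judged too high, the main change is still worth making.
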